### Recruitment and collection of baseline information

After cluster randomisation, sub-village leaders will identify all infants aged 6 months and their parents in a systematic door-to-door survey. Parents of identified infants will be invited to a meeting where the nature and purpose of the trial and eligibility criteria will be explained. Thereafter, the infants will be screened for eligibility. **Inclusion criteria** will be breastfeeding infants aged 6 months; parents (or caregivers) are residents in the sampled village and have no plans to move away during the intervention period. **Exclusion criteria** will be infants with obvious congenital or chronic abnormalities impairing feeding or physical growth measurements; have oedema; are severely ill or have clinical complications warranting hospitalisation. Parents/guardians and infants who meet the inclusion criteria, agree to participate in the trial and give a written informed consent will have their infants recruited in the trial. Baseline information of recruited infants and their parents/guardians will be collected using a structured questionnaire. The information will include household’s, parents’ and infant’s characteristics. Structured interviews with village and sub-village leaders will also be conducted to collect village information (i.e. population, health facility, water supply, schools, livelihoods, resources, economic opportunities).

### Ethical considerations and permissions

The trial will be explained in a formal letter and verbally to district administrative and health officials. Approval to include the selected villages in the trial will be sought from village authorities. After identification of eligible infants in each cluster, their parents/guardians will be invited to a meeting where nature and purpose of the trial will be explained. The information sheet and informed consent document will be tailored to the study group (intervention or control) to which a particular cluster was allocated [43]. Parents/guardians who agree to participate in the trial will be requested to sign a written informed consent. A verbal consent will be requested from parents or guardians who are unable to read and/or write. An impartial witness will be present when the verbal consent is given. Informed consent will also be sought from nutrition counsellors and health facility workers in intervention villages. During the course of the trial, infants reporting to be ill in both study groups will be referred to health facilities where they usually receive treatment free of charge according to Ministry of Health regulations. Households that do not participate in the intervention group will receive education and counselling resources at the end of intervention. Ethical clearance was obtained from the National Institute of Medical Research (Tanzania), Institute of Tropical Medicine (Belgium) and University of Antwerp (Belgium).

### The intervention

The language of communication during the intervention delivery will be Kiswahili, a written and spoken language in the country.

### Component 1: Education and counselling of mothers

This component aims to impart rural mothers and caregivers with action-oriented knowledge, skills, behaviour and attitude that will motivate their ability to adopt optimal infant and young child feeding and health care practices. Nutrition education and counselling will be conducted with mothers of recruited infants in three sessions. The first session will be conducted when infants are 6 months-old. The second and third sessions will be conducted when infants are aged 9 and 12 months, respectively. Each session is expected to last 2 to 3 hours. The content is consistent with age-specific feeding recommendations made by WHO [8, 44] and timed to coincide with child’s age at 6, 9 and 12 months. The sessions will be centred on feeding, health, hygiene and sanitation. Distribution of sessions and topic coverage is presented in Table 1. Theoretical sessions (Part 1) will be followed by cooking demonstrations (Part 2) and counselling for mothers who have individual concerns (Part 3).

**Table 1 Tab1:** **Education and counselling sessions for mothers when children attain different ages**

Session 1	Session 2	Session 3
Child 6 months-old	Child 9 months-old	Child 12 months-old
**Part 1:** Group education	Feedback and review of previously set goals	Feedback and review of previously set goals
	**Part 1:** Group education	**Part 1:** Group education
Breastfeeding your baby	Breastfeeding your baby	Breastfeeding your baby
Feeding your baby from 6 to 8 months (diversity, frequency, consistency, amount, responsive style)	Feeding your baby from 9 to 11 months (diversity, frequency, consistency, amount, responsive style)	Feeding your baby from 12 to 23 months (diversity, frequency, consistency, amount, responsive style)
Locally available foods for preparation of nutritious meals	Locally available foods for preparation of nutritious meals	Locally available foods for preparation of nutritious meals
Feeding your baby during and after illness	Feeding your baby during and after illness	Feeding your baby during and after illness
Hygiene (safety, handling & storage of food) and Home environment sanitation	Hygiene (safety, handling & storage of food) and Home environment sanitation	Hygiene (safety, handling & storage of food) and Home environment sanitation
Health care-seeking and Disease prevention	Health care-seeking and Disease prevention	Health care-seeking and Disease prevention
Utilisation of child health services and compliance to treatment and advice	Utilisation of child health services and compliance to treatment and advice	Utilisation of child health services and compliance to treatment and advice
**Part 2:** Cooking demonstration	**Part 2:** Cooking demonstration	**Part 2:** Cooking demonstration
**Part 3:** Individual counselling	**Part 3:** Individual counselling	**Part 3:** Individual counselling

Direct (teacher-directed), interactive (discussion, sharing) and experiential (learner-centred, activity-oriented) instructional strategies will guide the approach of delivering education sessions. Talks, group discussions, group work exercises, demonstrations, role plays, storytelling, simulation, case studies and problem solving will be used to impart knowledge and skills, enhance maternal attitude and self-efficacy. For example, the topic “Locally available foods for preparation of nutritious meals” will apply the following teaching methodologies:i.a lecture/talk will explain about nutrients in foods and their role in promoting growth and good health, and mothers will role play nutritional benefits;ii.group work will involve mothers in identification and grouping of locally available foods for making typical household meals;iii.mothers will be presented with case studies of meals to evaluate inadequacies, discuss and apply problem solving skills to overcome the inadequacies;iv.key recommendations (Table 2) for inclusion of varieties of foods to increase content and intake of nutrient density of meals will be summarised in a lecture and mothers encouraged to make implementation goals; andv.cooking demonstrations will show how food varieties can be used to prepare nutritious meals.

**Table 2 Tab2:** **Key recommendations and messages for promoting optimal feeding and health practices**

1	Continue to breastfeed your child on demand, during the day and night throughout the first and second years. Breastfeed first before giving other meals.
2	Start giving soft and thick meals in addition to breast milk when child completes 6 months, then continue with mashed and semi-solid meals. Increase variety, amount and consistency of food as he/she becomes used to eating and chewing different foods.
3	Prepare a thick porridge made from a combination of cereal flours. Enrich the porridge by adding groundnuts, milk, egg or legume. Thin porridge does not contain adequate nutrients to support your baby to grow well and stay healthy.
4	Give undiluted cow’s milk to your child at least 3 times per week.
5	Cook, mash, and add one or more ingredients from legumes (e.g. beans, pigeon peas, bambara groundnuts, cowpeas) in each meal.
6	Cook, mash and feed animal source foods (e.g. eggs, beef, pork, chicken, liver, fish, sardines) at least 3 times per week.
7	Cook, mash, and feed vegetables (e.g. leafy vegetables, pumpkin, avocado) in each meal.
8	Feed your child a fruit (e.g. pawpaw, ripe banana, mango, orange) after a meal at least once per day.
9	Increase frequency of feeding meals per day (2–3 times at 6–8 months, 3–4 times at 9–11 months, 3–4 times at 12–23 months). Feed 1–2 snacks (e.g. fruit, bread with groundnut paste) between two major meals.
10	Encourage your child to eat with patience and love. Encourage a sick child to drink and eat more frequently during illness. Provide extra food after illness to facilitate quick recovery.
11	Wash your hands with soap before preparing meals or before feeding children. Wash your hands with soap after visiting the toilet, and after cleaning a child who has defaecated.
12	Learn to recognise early danger signs and symptoms of childhood diseases. Promptly take a sick child to the nearest health facility for examination and treatment.
13	Ensure that your child completes a full course of prescribed medications. Return for a follow-up visit at the health facility when required or if child’s condition is not improving.
14	Keep your home environment clean. Use preventive measures to protect your child and family from diseases.

Cooking demonstrations aim to show how different food items can be used to prepare nutritious meals, illustrate appropriate amount and consistency of meals and demonstrate responsive feeding. Procedures for preparing nutritious meals based on promoted recipes will be described during the sessions. The recipes are based on meat, legumes, vegetables and root/tuber, and the foods can be eaten alone as a complete meal or eaten with cooked staple (stiff porridge *ugali*, rice, green banana, cassava). Under the guidance of the researcher, mothers of recruited infants and community-based nutrition counsellors will centrally prepare meals based on proposed recipes. One portion will be fed on-site and another given for feeding at home on the same day. Responsive feeding styles will be practiced by mothers during the feeding sessions and observed. For each cooking session, recipes will be alternated to reduce monotony, improve texture and flavour, and stimulate reflex chewing. Mothers will be encouraged to try the recipes and other feeding recommendations at home. Information booklets containing topic content, recipe examples and promoted recommendations will be distributed after the first session.

After cooking demonstrations, mothers will be invited for individual counselling. The counselling sessions will include listening, learning about their difficulties and assessing the situation, providing relevant information, and building mother’s confidence to modify behaviours and overcome barriers. The mother will be referred to nutrition counsellors in her village for support and follow-up during the monthly home visits. Follow-up visits at home will be done by community-based nutrition counsellors. After completion of each session (Part 1, 2, and 3), mothers will be encouraged to set achievable goals (i.e. to prompt intention to try the recommendations). Feedback regarding the set goals will be reviewed during the next education session.

### Component 2: Training community-based nutrition counsellors and monthly home visits

This component aims to empower community-based nutrition counsellors with action-oriented knowledge and skills to effectively counsel and negotiate with mothers and families to adopt recommended practices. In each intervention village, 2 individuals will be recruited and trained to carry out four major tasks: 1) counsel and support mothers and their families during home visits, 2) refer infants identified with danger signs of illnesses and malnutrition to health facilities, 3) supervise cooking demonstrations during the education sessions and 4) mobilise mothers for outcome assessments. Potential individuals will be nominated by village leaders in their respective villages, and the research team will interview and recruit the most suitable candidates. To be selected, a candidate has to be aged between 25 and 45 years, be a resident in the village with no plans of leaving within a year, has completed at least 7 years of formal education and has personal experience in infant feeding. In addition, the candidate will have to demonstrate that they have time, are eager to participate in the trial and willing to undertake home visits.

All recruited nutrition counsellors will be centrally trained for 3 days. The first training session will be conducted at the beginning of the intervention whereas the second session of similar content will be repeated 6 months later (i.e. when infants are aged 12 months). The training will contain three modules. **Module 1** will focus on orientation and introduction, why nutrition matters during the first two years of life, feeding principles and practices, use of locally available foods to make nutritious complementary meals, child health and preventive measures. **Module 2** will focus on communication skills, behaviour change communication, counselling skills and negotiation, problem solving (trying different solutions to common problems), use of counselling resources, field practice and feedback on field practice. **Module 3** will focus on home visits tasks and procedures, use of counselling resources, supervisory visits and training evaluation. A standardised test with multiple and open-ended questions will be given before and after training to test knowledge and attitudes about child feeding and health. The training methodology will include lectures, small group activities and discussions, plenary discussions, demonstrations, role plays, and hands-on field practice with mothers in villages which will not be part of the intervention. Theoretical training will be followed by practical exercises designed to test performance. During the practice sessions, they will be observed and their skills discussed for improvement during plenary sessions. After training, counsellors will be issued counselling resources (counselling cards, workbook, family card, referral slip, counselling manual) as home visiting tools.

The nutrition counsellors will begin home visits immediately after their training. Each nutrition counsellor will be assigned 10–12 mothers residing in their village and each mother will be individually visited and counselled. They will make home visits once per month for 9 months of the intervention period. Mothers with sick children or children with feeding problems will be offered additional visits. The counselling will take place at home to ensure other family members can also take part in the sessions. The counsellors will be responsible for keeping home visits records in workbooks. These will include:

behaviour adopted by mothers;issues discussed, barriers, next/missed appointments;referrals to health facilities given to infants with danger signs of childhood illnesses; andin-depth information of best-case and worst-case household circumstances for lessons learned during the intervention.

Achievements and unresolved difficulties during the visits will be discussed during supervisory or monitoring visits.

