### Sampling and randomisation

A village forms a unit of randomisation for the trial, while infants and their parents within the village will form units of observation. Two out of three Divisions (Kibakwe, Mpwapwa, Rudi) in the district will be selected by simple random sampling. A list of all villages in the selected divisions will be compiled, and villages found to have an on-going intervention or project will be excluded. Eighteen villages will be selected from the list by simple random sampling. The preselected villages will be listed alphabetically. A simple randomisation with a 1:1 allocation will be used to randomise villages to either control or intervention group. A list of random numbers will be generated in MS Excel 2007 and the generated values will be fixed by copying them as “values” next to the alphabetic list of the preselected villages. These will then be arranged in ascending order according to the generated random numbers: and the first 9 will be selected as intervention clusters and the last 9 as control clusters.

Generation of allocation sequence and randomisation of clusters will be done by a statistician blinded to study groups and not participating in the research. Data collectors will be masked of the village allocation by not informing them of the allocation, not being part of trial implementers and not being residents in any of the villages. However, trial participants may know if they are in the intervention or control group.

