### Sample size estimate

The sample size was calculated for unmatched cluster-randomised trials [41] as follows:

whereby: **c** is the number of clusters required in each treatment group; **Z**_**α/2**_ is the standard normal distribution corresponding to the 95% degree of confidence on a two-sided test; **Z**_**β**_ is the standard normal distribution corresponding to 80% power; **σ**_**0**_ and **σ**_**1**_ are the within cluster standard deviations of the outcome variable in the presence and absence of intervention, respectively; **n** is the minimum number of individuals sampled in each cluster; **k** is the coefficient of variation of true means between clusters within each group; and **μ**_**0**_ and **μ**_**1**_ are the within cluster population means in the presence and absence of intervention, respectively.

As there is no information available on the intra-cluster coefficient of variation, the estimate for the between-cluster coefficient of variation (k) was based on conservative estimates of ≤0.25 and 0.15-0.25 experienced in similar health and nutrition studies [41, 42]. A coefficient of variation between clusters (k) of 0.1 was assumed and 30 infants per cluster based on district’s estimates of birth rates. Data from the 2009 formative survey were used to make assumptions on change of values of the primary outcome length-for-age Z-scores (LAZ): a mean LAZ of −1.5 and a standard deviation of 1.3 in the control group. From the formula, 8.9 (~9) clusters will be needed to detect at least a 0.35 difference in LAZ between intervention and control groups, with the power of 80% (Z_β_ = 0.84) and a statistical significance of 5% (p < 0.05; Z_α/2_ = 1.96, two-tailed test). A total of 270 infants will be enrolled in each study group. Allowing for a 10% loss to follow-up, a sample size of 297 infants, i.e. 33 per village, will be required. A total of 594 (~600) infants will be recruited.

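### Two counsellors per village with 10–12 mothers each give 20–24 home-visit places, but 33 infants per village are to be enrolled: the three figures cannot all hold

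*Protocol article*

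**What the plan says.** Three figures bear on this point, all in the protocol article.

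- **Counsellors per village** (Component 2): "In each intervention village, 2 individuals will be recruited and trained to carry out four major tasks".
- **Caseload** (same section): "Each nutrition counsellor will be assigned 10–12 mothers residing in their village and each mother will be individually visited and counselled". Visits are monthly over the 9-month intervention.
- **Enrolment per village** (Sample size estimate): "Allowing for a 10% loss to follow-up, a sample size of 297 infants, i.e. 33 per village, will be required". The calculation behind it uses 30 per village: "A coefficient of variation between clusters (k) of 0.1 was assumed and 30 infants per cluster based on district’s estimates of birth rates".

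The Sampling and randomisation section gives nine intervention villages: "the first 9 will be selected as intervention clusters and the last 9 as control clusters".

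Study design describes the counsellors' monthly visits to mothers and families in the intervention group without exception. Component 1 refers mothers to the counsellors of their own village for follow-up and gives the home follow-up to those counsellors. Table 4 marks home visits in every month from age 6 to age 15 months. No section provides further counsellors, other home visitors, or a subset of enrolled mothers who receive no visits.

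**The concern.** Training of counsellors and monthly home visits form one of the four components of the package, and the only one that brings individual contact every month. If two counsellors each take 10–12 mothers, there are fewer places than enrolled mothers in every intervention village.

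Two things follow if the caseload is applied as a ceiling. First, the analysis is by intention to treat, so mothers without a counsellor still count in the intervention arm and pull the estimated effect towards zero. The Sample size estimate section powers the trial for a 0.35 difference in LAZ and makes no allowance for partial delivery. Second, Data management and analysis plans to compare outcomes between high and low scorers on process characteristics within the intervention arm. If some mothers score low because no place existed for them, and no rule says who they are, that comparison could be confounded by however the places were given out.

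**Working it through.** **1. The plan's enrolment figures.** 9 villages × 30 = 270, as stated ("A total of 270 infants will be enrolled in each study group"). 270 × 1.10 = 297, and 297 / 9 = 33 per village. Two arms give 2 × 297 = 594 ("A total of 594 (~600) infants will be recruited"). All of these reproduce. I assume one mother per infant.

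**2. Home-visit places.** Per village: 2 × 10 = 20 to 2 × 12 = 24. Per arm: 9 × 20 = 180 to 9 × 24 = 216.

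**3. Shortfall at different enrolments.**

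| Infants per village | Source | Short per village | Share |
|---|---|---|---|
| 33 | stated enrolment | 9–13 | 27.3–39.4% |
| 33.3 | 600 / 18 | 9.3–13.3 | 28.0–40.0% |
| 30 | sample size calculation | 6–10 | 20.0–33.3% |
| 27 | 30 less 10%, an assumption | 3–7 | 11.1–25.9% |

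At arm level, 297 − 216 = 81 and 297 − 180 = 117. The gap remains in every row.

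**4. What would close it, as arithmetic only.** With two counsellors, 33 / 2 = 16.5 mothers each. At 10–12 mothers each, 33 / 12 = 2.75 to 33 / 10 = 3.3 counsellors per village.

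**5. Illustration of dilution.** The share of the effect carried by home visits is not in the documents. Suppose uncovered mothers gain half the effect:

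- 0.35 × (216 + 0.5 × 81) / 297 = 0.302
- 0.35 × (180 + 0.5 × 117) / 297 = 0.281

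For power I used the standard unmatched-cluster formula, because the plan's own formula is not legible in the text available:

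c = 1 + (z_α/2 + z_β)² × [2σ²/n + k²(μ0² + μ1²)] / d²

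Solved for z_β with c = 9, n = 30, k = 0.1, σ = 1.3 in both arms, μ0 = −1.5 and μ1 = −1.5 + d:

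- d = 0.35: bracket = 0.1127 + 0.01 × (2.25 + 1.3225) = 0.1484; z_β = √(8 × 0.1225 / 0.1484) − 1.96 = 0.61; power about 73%.
- d = 0.30: bracket = 0.1127 + 0.01 × (2.25 + 1.44) = 0.1496; z_β = √(8 × 0.09 / 0.1496) − 1.96 = 0.23; power about 59%.
- d = 0.28: bracket = 0.1127 + 0.01 × (2.25 + 1.4884) = 0.1501; z_β = √(8 × 0.0784 / 0.1501) − 1.96 = 0.08; power about 53%.

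The right comparison for 53–59% is the undiluted 73% from the same formula, not the 80% stated in the plan. The distance from 80% to 73% is a separate sample size question and is not caused by the caseload.

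**The case against.** The strongest reply is that the protocol intends every mother to be visited. Study design, Component 1 and Component 2 all read that way, so the likeliest explanation is that the caseload or the counsellor number was never brought into line with the sample size. A reader might infer that the trial plans to leave 27–39% of intervention mothers without a counsellor. The documents do not support that: they show that three figures conflict, not which one gives way. This part of the objection stands.

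Three other strong readings also fail.

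- **No benefit at all for uncovered mothers.** They would still have three education sessions with cooking demonstrations and individual counselling, the information booklet, the family sensitisation meetings and, where a facility exists, sensitised health staff. A zero-effect scenario is not a reasonable bound.
- **Damage to the reach and dose indicators.** Table 3 counts home visits conducted and mothers visited, so these indicators would reveal a shortfall. Only the high-versus-low comparison is exposed.
- **Bias in the randomised comparison.** Incomplete delivery would dilute the intention-to-treat effect; it would not invalidate the comparison. Nor does the article say how, or by whom, places would be allocated if they ran short.

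The objection does not remove the contradiction. Losses to follow-up do not close the gap, and none have occurred when visits start right after training. Staggered entry does not close it either: the second training falls when infants are 12 months old, so the schedule follows a single cohort. Spare capacity in another village cannot be used, because counsellors are assigned mothers from their own village.

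**Conclusion.** The point holds as an internal contradiction. Two counsellors, 10–12 mothers each and 33 enrolled infants per village cannot all be true. Read literally, they leave 9–13 mothers per village, 81–117 of 297 (27–39%), on no list, and 20–33% at 30 per village. These shares rest only on figures in the article and on one mother per infant.

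The effect on power is conditional. It arises only if the caseload is applied as written, and its size depends on the unknown share of benefit carried by home visits. The fall from about 73% to 53–59% illustrates one assumption (half the effect) and is not an estimate. The randomisation, primary outcome and analysis model are unaffected. This should be fixed, but it does not threaten the validity of the design.

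**What to change.** Reconcile the number of counsellors and the caseload in Component 2 with the enrolment in the Sample size estimate section, so that every enrolled intervention mother is on a named counsellor's list. Which figure changes is for the sponsor to decide. The arithmetic in step 4 (16–17 mothers for each of two counsellors, or about three counsellors at 10–12 each) only shows what consistency requires.

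Only if some enrolled mothers are deliberately to have no home visits should the protocol state how they are chosen and restate the effect size for which the trial is powered.

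The cost is a wording change and one staffing or caseload decision: a heavier load per counsellor, or additional counsellors to recruit and train. Timing matters, because Trial status and schedule of intervention activities puts counsellor training first, before infants are recruited. Changing the arrangement after that would mean further training or a change in delivery during the trial.
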